[20 Dissemination and intellectual property 18](#_Toc86830258)

[References 19](#_Toc86830259)

List of abbreviations

ADE Adverse Device Effect

AE Adverse Event

CERC Clinical Eye Research Centre

CRF Case Report Form

ECD Endothelial cell count

FMEA Failure Modes and Effects Analysis

GCP Good Clinical Practice

FECD Fuch’s Endothelial Corneal Dystrophy

LIVE-OCT Liverpool Optical Coherence Tomography

LUHFT Liverpool University Hospitals NHS Foundation Trust

OCT Optical Coherence Tomography

PIS Patient Information sheet

REC Research Ethics Committee

SADE Serious Adverse Device Effects

SAE Serious Adverse Event

SPEU St Paul’s Eye Unit

UoL University of Liverpool

USADE Unanticipated Serious Adverse Device Effect

1. Study summary

| Study Title | Clinical Evaluation of a Novel LiveOCT Device to Improve the Management of Eye Disease | |
| --- | --- | --- |
| Internal ref. no. (or short title) | LiveOCT Study | |
| Clinical Phase | Na | |
| Study Design | Prospective Observational Study | |
| Study Participants | Patients aged 12 years and above with a diagnosis of either keratoconus or Fuchs endothelial corneal dystrophy (FECD) and/ or corneal lamellar surgery and subjects with no corneal disease (healthy volunteers). | |
| Planned Sample Size | 40 patients with keratoconus, 30 with FECD and/or corneal lamellar surgery, and 20 with no known corneal abnormalities (healthy volunteers). | |
| Treatment duration | N/A | |
| Follow up duration | Baseline and follow up 3 months and 6 months | |
| Planned Study Period | *1^st^ May 2021 to 30^th^ Oct 2022* | |
|  | Objectives | Outcome Measures |
| Primary | To compare image quality | The quality of the LiveOCT images from 2 variants (D1 and D2) will be compared with the existing models according to predefined diagnostic image criteria. |
| Secondary | To assess repeatability of image quality  Sensitivity  Assess cost effectiveness  Patient experience |  |
| Medical device | Liverpool Optical Coherence Tomography device (LiveOCT). | |
| Formulation, Dose, Route of Administration | Na | |

1. Background

Optical coherence tomography (OCT) has been widely used in the management of eye disease. Commercially available OCT systems are still unable to meet the increasing demand posed by clinical decision-making. With an i4i grant, we have in Liverpool invented a new OCT device. This has enabled us to achieve in vitro in human corneas an improved resolution down to 2.1 microns. While the OCT device worked well in its current form in the laboratory, we were to yet translate this application into clinical practice and potentially provide benefit to patients. This translation required relevant in vivo device optimisation and improvement as well as clinical studies to demonstrate its potential to help improve the management of ophthalmic diseases.

1. Rationale

In our current i4i project (Ref: II-LA-1116-20008), we are planning to address this by realising a novel clinically proved OCT device that makes use of new technologies and approaches that can be used on human subjects. Having designed and built the device, we hope to evaluate and optimise the device and data analysis on both healthy volunteers and patients with various cornea diseases. The project will ultimately bring significant benefits for people with eye disease, improving healthcare, and subsequently reducing social and economic costs. We have developed a proof-of-concept observational study protocol to demonstrate clinical utility for diagnosis, disease classification and management. We will examine the performance of our LiveOCT device with comparison to current clinically used devices (corneal topography and tomography devices including OCT and ultrasound) with particular regard to intra, inter-observer and inter-device variability. This will be used to determine precision and accuracy, the latter based on currently accepted clinical standards. In comparison with other standard techniques, we hope to identify the uniqueness of our LiveOCT for supporting improved diagnosis, monitoring and treatment of eye diseases. We have developed 2 slightly different variants of our LiveOCT device, device 1 (D1) and device 2 (D2). The only difference between the variants is a very slight modification of the internal optics, which results in different image properties. There will be no difference in operation or patient experience between the variants.

1. Objectives and outcome endpoints/measures

## Objectives

### Primary objective

- To compare the quality and information provided of corneal images obtained with the new LiveOCT device variants (D1 and D2) with those obtained using standard clinical instruments including existing OCT devices.

### Secondary objectives

- To evaluate repeatability, sensitivity and specificity of the LiveOCT device.
- To evaluate costs and consequences- from an NHS perspective we will explore the costs and consequences of the LiveOCT device as compared to usual care.
- To study patient experience on LiveOCT device.

1. Study design

This study will follow a prospective observational study design. The single study site is St. Paul’s Eye Unit, The Liverpool University Hospitals NHS Foundation Trust (LUHFT).

Following recruitment, eligibility assessments and consent, participants will undergo a baseline assessment. Follow up assessments will take place after 3 and 6 months.

During each visit, the participant will undergo standard eye examinations (visual acuity and slit-lamp bio microscopy), and non-invasive tests including endothelial cell counting (ECD), tomography, and OCT imaging by standard OCT devices (TOMEY CASIA SS-1000 and Heidelberg Spectralis) and our new LiveOCT device variants (D1 and D2). Two qualified individuals, both operating one of two LiveOCT devices equipped with the study software, will perform the study device measurements. Each patient will be measured three times with each device at both the baseline and at follow-up visits (after 3 and 6 months). See figure 1 for the study design showing the study design/ patient pathway.

We expect the duration of D1 and D2 assessments (capturing 3 images on each device per visit) to take 15 minutes for each device, so 30 mins in total will be dedicated to our novel OCT devices each visit. The order of the OCT devices will be randomised using a random permutation approach to avoid bias through patient or investigator fatigue but the all measurements on each device will take place at the same time as to avoid delays caused by positioning the patient.

   
[figure not shown]

Figure 1. Schematic of the Study design/ patient pathway

1. Study setting

The Study will run in a single site at the Clinical Eye Research Centre (CERC) in St. Paul’s Eye Unit within The Liverpool University Hospitals NHS Foundation Trust (LUHFT).

1. Study participants

## Overall description of study participants

90 subjects 12 years old and above who meet the inclusion and exclusion criteria will be recruited and subsequently tested at the cornea clinics of St Paul’s Eye Unit (SPEU), LUHFT. There will be 3 groups of participants: 40 patients with keratoconus, 30 with FECD and/or corneal lamellar surgery, and 20 with no known corneal abnormality.

## Inclusion criteria

Patients, male or female, aged 12 years and above with a diagnosis of either keratoconus or Fuchs endothelial corneal dystrophy (FECD)/ corneal lamellar surgery and subjects with no corneal disease (healthy volunteers).

## Exclusion criteria

In this study, patients who have poor fixation or have a learning disability will not be excluded as this will be an opportunity to hopefully demonstrate the advantage of our new LiveOCT device. Exclusion criteria: Nystagmus, under 12 years old, inability to provide informed consent,

1. Study procedures

## Screening and eligibility assessment

Eligible patients and their guardians (if appropriate) attending the corneal clinics, will initially be approached by members of the direct clinical care team and given an A4 advert for our study. If interested, a simple eligibility assessment will be carried out. If eligible, they will be asked if they would be willing to be contacted by a member of the study team to discuss further. If agreeable, they will be given the participant information sheet (PIS) and told they will be contacted subsequently by an investigator.

## Informed consent

When contacted, potential participants will be taken through the information sheet and given opportunity to ask questions. Written and verbal versions of the participant information and Informed consent will be presented to the participants detailing no less than: the exact nature of the study; the implications and constraints of the protocol; the known side effects and any risks involved in taking part. It will be clearly stated that the participant is free to withdraw from the study at any time for any reason without prejudice to future care, and with no obligation to give the reason for withdrawal.

For people with learning disabilities their legal guardian will be asked to witness and or give consent on their behalf after they have shown they have understood the information provided in the PIS and consent form.

The decision to include children (12 years old and above) in this study was made because this is the age when Keratoconus may start and we are hoping to observe the initial changes caused by this condition. The legal guardian/ parent of the child will be asked to give consent on their behalf after they have shown they have understood the details provided in the PIS and consent form. The child will be involved in the decision-making process as much as possible and will be asked to give assent.

The participant will be allowed up to 2 weeks to consider the information and the opportunity to question the Investigator, their GP or other independent parties to decide if they would like to participate in the study. Written Informed Consent will then be obtained by means of participant dated signature and the dated signature of the person who presented and obtained the informed consent, using the latest approved version of the informed consent form. The person who obtained the consent must be suitably qualified and experienced and have been authorised to do so by the Chief Investigator according to the ethically approved protocol, principles of Good Clinical Practice (GCP) and Declaration of Helsinki. A copy of the signed Informed Consent will be given to the participants. The original signed form will be retained at the NHS research site.

The study will be carried out by following UoL and LUHFT guidance and policy associated with COVID-19, as well as the Government’s COVID-19 guidance and law. Social distancing and face covering guidelines will be followed as appropriate to keep both researchers and participants safe. All participants will be recruited from scheduled appointments at the clinics at St Paul’s Eye Unit.

## Baseline and subsequent assessments

For each participant, there will be 3 visits: baseline, month 3 and month 6. During each visit, the participant will undergo standard eye examinations (visual acuity and slit-lamp bio microscopy), and non-invasive tests including endothelial cell counting (ECD), tomography, and OCT imaging by standard OCT devices (TOMEY CASIA SS-1000 and Heidelberg Spectralis) and our new LiveOCT device variants. Two qualified individuals, both operating one of two LiveOCT devices equipped with the study software, will perform the study device measurements. Each patient will be measured three times with each device at both the baseline and at follow-up visits. A questionnaire will be completed on their experience and view of the device at the end of each visit.

The following procedures will be carried out on each patient at baseline, month 3 and month 6, as shown in Table 1:

1. Eye examinations (visual acuity and slit-lamp bio microscopy)
2. Endothelial cell counting (ECD) with confocal microscopy
3. Tomography with Pentacam camera
4. OCT imaging with devices currently in clinic (The TOMEY Casia and Heidelberg Spectralis)
5. Imaging by our new LiveOCT device – variant 1 (D1) and 2 (D2)
6. Patient experience questionnaire

The order of the OCT devices will be randomised using a random permutation approach to avoid bias through patient or investigator fatigue but the all measurements on each device will take place at the same time as to avoid delays caused by positioning the patient.

All the procedures except for imaging with our new LiveOCT device are part of standard care. For patients with keratoconus, all the three visits are standard patient care pathway. For patients with FECD, month 3 visit is an additional visit to the standard care. For healthy volunteers, all the 3 visits will be research activities.

**Table 1: Tests undertaken during each of the three visits.**

|  | **Baseline (month 0)** | **Month 3 Visit** | **Month 6 visit** | **Comments** |
| --- | --- | --- | --- | --- |
| **Eye examination (visual acuity and slit lamp bio microscopy)** | V | V | V | Standard Clinical procedure |
| **Endothelial cell counting (ECD)** | V | V | V | Standard Clinical procedure |
| **Tomography** | V | V | V | Standard Clinical procedure |
| **Tomography** | V | V | V | Standard Clinical procedure |
| **Imaging using our new LiveOCT devices, D1** | V | V | V | Extra test |
| **Imaging using our new LiveOCT device, D2** | V | V | V | Extra test |
| * All the procedures except for imaging by using our new OCT device are part of standard care pathway  * For patients with Keratoconus, all the three visits are standard patient care pathway  * For patients with FECD, month 3 visit is an additional visit to the standard care  * For healthy volunteers, all 3 visits will be research activities | | | | |

1. Study treatments

## Description of study intervention(s)

*In vivo* non-contact imaging of the layers of the cornea using a new anterior segment LiveOCT imaging device. 2 slightly different variants will be used. The only difference between variant 1 (D1) and variant 2 (D2) will be a small modification to the internal optics with no difference to user or patient experience.

## Maintenance and storage of device

The device will be stored in the study room, which will be locked when not in use. It does not need to be kept in special conditions. The device will be monitored and maintained by the team throughout the clinical study.

1. Proposed outcome measures

## Primary outcomes

**Image quality**: The quality of the LiveOCT images will be compared with the existing models according to predefined diagnostic image criteria.

**Added information:** The anticipated additional information provided by our LiveOCT will then be used to determine if and what changes have occurred in the patients with FECD and keratoconus that were not apparent with the standard tests and whether these changes reflect or indicate change (deterioration or improvement) in the status of the disease. We will also determine which additional components of the cornea have been affected and whether and to what extent are the features reproducible. An evaluation will also be undertaken to determine whether the information provided by our LiveOCT is associated with specific features evident in the images from the standard instruments and whether the information is new or redundant.

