## Secondary outcomes

**Repeatability/reproducibility:** Outcome metrics will be the repeatability and reproducibility of measurements (identification and thickness) of structural parameters of the cornea, corneal surface contour and refractive power.

**Sensitivity and specificity:** We will use published grading systems specific to the two main conditions of FECD and keratoconus. For keratoconus, the sensitivity of the LiveOCT will be assessed by its ability to detect the same diagnostic parameters of non-uniform and focal corneal thinning and irregular and non-asymmetric anterior and posterior corneal profiles currently measured using the Pentacam. For FECD, the sensitivity of the LiveOCT will be assessed by its ability to measure increases in corneal thickness and areas of corneal swelling, and excrescences (guttata) and thickening of Descemet's membrane in patients who have guttata evident with slit lamp bio microscopy and increased corneal thickness measured with the Pentacam. Specificity will be defined as the percentage in which the described diagnostic changes in the cornea for keratoconus and FECD are not apparent with the LiveOCT device.

**Patient experience:** Study participants will be asked to fill in a simple set of questions concerning their experience with the LiveOCT devices. The patients will be asked to fill out paper copies of the questionnaire after the end of each study appointment, but the study nurse will be available to help if required.

If the participant indicates that they are feeling particularly anxious or depressed on the questionnaire, a member of their care team will pass this information onto their GP.

**Cost Effectiveness:** See 13.3 - economic evaluation

1. Definition of end of study

The study will be completed and terminated on 31st October 2022, which is defined to be the date when analysis of the data collected during the trial is being completed.

Suspension or early termination of the study when there are serious concerns about subjects’ safety and inadequate performance, that cannot be mitigated by modifications of the study protocol based upon the review of the safety data.

1. Discontinuation/ withdrawal of participants from study treatment

If a decision is made by the participant and or/clinician not to continue with the study, the participant will be removed from it and the event recorded. Data will still be collected unless the participant explicitly withdraws consent for it.

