## Access to data

Identifiable information will only be accessed by the authorised research team at the NHS research site. Any participant information (e.g. images and questionnaires) will be pseudo-anonymised within the LUHFT before being transferred to the universities for analysis, and stored securely at the university’s secured network drive. Pseudo anonymised data related to health economics analysis will be shared with [name] [name] at Bangor University.

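### The protocol specifies no masked reading for its reader-judged outcomes: image quality, added information, and the visual signs used for sensitivity

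*Protocol*

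**What the plan says.** Under Primary outcomes, the protocol compares image quality between LiveOCT and the existing devices: "The quality of the LiveOCT images will be compared with the existing models according to predefined diagnostic image criteria". The criteria are not listed there.

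The second primary outcome, added information, is to be "used to determine if and what changes have occurred in the patients with FECD and keratoconus that were not apparent with the standard tests". The same section then asks "whether the information provided by our LiveOCT is associated with specific features evident in the images from the standard instruments", so that the information can be classed as new or redundant.

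Under Secondary outcomes, sensitivity in keratoconus is judged by "its ability to detect the same diagnostic parameters of non-uniform and focal corneal thinning" and by irregular corneal profiles, with the Pentacam as reference. In FECD the signs, including guttata and Descemet's membrane thickening, are sought "in patients who have guttata evident with slit lamp bio microscopy and increased corneal thickness measured with the Pentacam".

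Two provisions bear on bias or on what a reader sees:

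- **Study design**, repeated under Baseline and subsequent assessments: "The order of the OCT devices will be randomised using a random permutation approach to avoid bias through patient or investigator fatigue".
- **Data collection tools** and **Access to data**: each participant has one study ID that indexes all their data. LiveOCT exports for analysis drop notes and identifying details but keep that ID. Images and questionnaires "will be pseudo-anonymised within the LUHFT before being transferred to the universities for analysis".

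No section mentions masking, reading order, independent readers, or who scores the images.

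**The concern.** Scoring quality, deciding that LiveOCT shows a change the standard tests missed, and calling a guttata present are all judgements. If the reader knows which device produced the image, which visit it came from, what disease the patient has or what the reference test showed, that knowledge can move borderline calls. The protocol recognises bias at acquisition and guards against it, but has no matching guard at the reading step, where these outcomes are created.

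Three results are exposed:

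- **The quality comparison**, to knowledge of the device. The quality score is also the primary outcome measure in the health economics data plan (Table 2), so any bias carries into the cost-consequences analysis.
- **The added-information outcome**, to knowledge of visit order and of the standard results. A false change call on LiveOCT counts directly as added information.
- **FECD sensitivity**, to knowledge of the reference result. Every patient assessed is already positive on the reference tests, so an unmasked reader knows the expected answer.

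**Working it through.** **What each safeguard covers**

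| Provision | Acts on | Leaves open |
| --- | --- | --- |
| Random device order (Study design) | Fatigue of patient or operator during imaging | Everything the reader knows later |
| Pseudonymisation (Access to data) | Patient identity | Device, diagnosis, visit, reference result |
| Removal of notes at LiveOCT export (Data collection tools) | Free-text clinical content | Study ID, which links to the rest of the record |
| Predefined criteria, published grading systems (Primary and Secondary outcomes) | Consistency of scoring | Borderline calls by a reader who knows the context |
| Steering committee (Monitoring) | Adherence, data recording, adverse events | Image reading, which is not assigned to it |

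None of these supplies a masked read.

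**Size**

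The protocol states no reader-error figure, so there is none to reproduce. The two illustrations below rest on assumed rates and are given as ranges.

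*1. Sensitivity for a visual sign such as guttata.* Assume a share e of reference-positive patients has an equivocal sign on LiveOCT and the rest are clear positives. Assume a masked reader calls half the equivocal signs present, and a reader who knows the reference result calls a share u.

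Masked sensitivity = (1 − e) + 0.5e. Unmasked sensitivity = (1 − e) + u·e. Shift = e(u − 0.5).

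| e | Masked | Unmasked, u = 0.75 | Unmasked, u = 1 | Shift in points |
| --- | --- | --- | --- | --- |
| 10% | 95% | 97.5% | 100% | 2.5 to 5 |
| 20% | 90% | 95% | 100% | 5 to 10 |
| 30% | 85% | 92.5% | 100% | 7.5 to 15 |

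The shift depends on the share e and not on the number of patients. It therefore does not matter that the group of 30 also includes lamellar-surgery patients who may not have guttata.

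*2. False added information in keratoconus.* The Sample size calculation section expects 20% of 40 patients to change on the Pentacam: 0.20 × 40 = 8, as the protocol states. That leaves 40 − 8 = 32 without change. Borrow this 20% as the true rate of change for a reader-judged feature. Assume LiveOCT finds all 8, shows no real extra change, and is over-called in a share x of the 32.

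Expected false LiveOCT-only calls = 32x. If the paired calls were compared by an exact McNemar test (also an assumption, since the protocol names no test for this outcome), all discordant pairs would favour LiveOCT. Five such pairs give p = 2 × 0.5^5 = 0.0625 and six give p = 2 × 0.5^6 = 0.031, so six or more are significant at two-sided 0.05. The chance of that is P(X ≥ 6) with X ~ Binomial(32, x).

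| x | Expected false calls | Chance of a falsely significant result |
| --- | --- | --- |
| 5% | 1.6 | 0.5% |
| 10% | 3.2 | 9% |
| 20% | 6.4 | 64% |
| 30% | 9.6 | 95% |

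With the 36 patients expected after dropout (29 without change), the chances are 0.3%, 6%, 54% and 91%. Low over-call rates do little harm. From about 20%, reading alone could produce a positive result.

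**The case against.** The strongest reply is that the protocol is silent, not wrong. It never says that reading is unmasked. It refers to predefined criteria, a data management plan and associated documents that are not shown, and reading rules could be there. It removes notes at export, and it describes the study as proof of concept. The Sample size calculation section also names change in thinnest corneal thickness as the primary endpoint. That is a numeric measurement, and the keratoconus parameters are likewise largely measured and graded by published systems.

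Much of this stands, and it sets the limits of the point. What can be said is that no masked reading is specified, not that reading is known to be unmasked. The thickness endpoint is less exposed, so the point is confined to image quality, added information and visual signs. It is still a matter for the protocol: what a reader may know is study conduct, to be settled before scoring, and is not something an analysis plan normally supplies.

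A reader might infer four stronger things that the document does not support:

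- **That the inventors score the images.** The Background says "we have in Liverpool invented a new OCT device", and data go to the University research team and the universities for analysis. No reader is named and no scoring site is given, so the link is an inference.
- **That D1 and D2 could be fully masked to each other.** The protocol says they do not differ for operator or patient, but the Rationale says their image properties differ.
- **That specificity is inflated too.** The Secondary outcomes section gives no healthy-group denominator for specificity, so no direction of bias can be asserted.
- **That the damage would be permanent.** Data and the software to read them are archived for 15 years, so a masked re-read would remain possible.

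**Conclusion.** The point holds as an omission that leaves the outcomes in the Primary outcomes section, and the visual signs used for sensitivity, open to reader bias. It is worth correcting because these judgements carry the comparison the study is built around and a better method is available at small cost.

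The size is unknown. The ranges of 2.5 to 15 points for sensitivity, and of 0.5% to 95% for a falsely significant change comparison with 40 patients, come entirely from assumed equivocal shares, call rates and over-call rates. They show that the effect could be anything from negligible to decisive. They do not estimate what will happen. If masked reading is already set out in one of the associated documents, the protocol needs only to say so.

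**What to change.** State in the Primary outcomes and Secondary outcomes sections that:

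- images from LiveOCT and from the comparator OCTs are recoded and read in random order, with study ID, disease group, visit date and device label removed;
- LiveOCT calls are locked before the reader sees any Pentacam, slit-lamp or endothelial cell result, and the new-versus-redundant comparison is made only after that lock;
- where change between visits is judged, the two visits of a pair are read in masked time order;
- the report says how far masking to device succeeded.

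**Cost.** A recoding step is needed for each device's images. The export described in the protocol belongs to the LiveOCT software, and the Casia and Spectralis images are not described as passing through it, so they need their own step. A locked scoring sheet is also needed. No extra patients, visits or imaging are required.

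**Limitation.** Masking to device may be incomplete, for LiveOCT against the commercial OCTs and possibly for D1 against D2, because image properties differ. The remedy is therefore weakest for the quality comparison. Withholding visit and reference result remains feasible, and so does withholding the diagnosis label.

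### The added-information primary outcome, as worded, omits changes LiveOCT misses and does not use the healthy volunteers, so it cannot separate real gain from false LiveOCT change

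*Protocol*

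**What the plan says.** The protocol's Primary outcomes section lists image quality and added information. For the second, the extra information expected from LiveOCT is used to "determine if and what changes have occurred in the patients with FECD and keratoconus that were not apparent with the standard tests", and then to judge whether such changes point to a better or worse disease state. The same paragraph asks "whether and to what extent are the features reproducible", and ends by asking how the LiveOCT information relates to features on the standard instruments and "whether the information is new or redundant".

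The Primary objective is neutral in direction: it compares the quality and information of LiveOCT images with those from standard instruments.

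The groups are "40 patients with keratoconus, 30 with FECD and/or corneal lamellar surgery, and 20 with no known corneal abnormality". Under Baseline and subsequent assessments, every participant has LiveOCT and standard imaging at months 0, 3 and 6, and "For healthy volunteers, all the 3 visits will be research activities". The Sample size calculation gives the healthy group one role, to supply LiveOCT reproducibility data.

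**The concern.** A comparison of two methods has two kinds of disagreement. This outcome names one of them. A change that the Pentacam or slit lamp shows and LiveOCT does not has no place in it, because the closing classification offers new or redundant but no category for lost. The outcome therefore delivers less than the two-way comparison of information that the objective promises.

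The second gap is the missing reference rate. A change seen only on LiveOCT has, by definition, no standard test to confirm it. It may be real, or it may come from repositioning, drift or artefact between visits. A group not expected to change would show how often such calls arise without disease. That group is in the study, but this outcome does not use it. A count of LiveOCT-only changes in patients would then have nothing to be judged against.

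**Working it through.** **1. What is counted.** For a given feature in a given patient, change falls in one of four cells:

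| | Standard: change | Standard: no change |
|---|---|---|
| LiveOCT: change | both | LiveOCT only (named by the outcome) |
| LiveOCT: no change | standard only (not named) | neither |

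The redundancy question bears on the first cell. No sentence of the outcome bears on the standard-only cell, and no sentence names the healthy group.

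**2. The plan's own figure.** The Sample size calculation compares 20% with 50% at alpha 0.05 and beta 0.2. With two independent proportions, unpooled variance and a two-sided test, n = (1.960 + 0.842)² × (0.2×0.8 + 0.5×0.5) / 0.3² = 35.76, rounded up to 36. With 10% dropout, 36 / 0.9 = 40. The stated 36 and 40 reproduce. They concern change in thinnest corneal thickness (TCT), not added information, so they do not settle this point, but they show where the benefit is expected.

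**3. Size of the LiveOCT-only cell on the plan's figures.**
- Pentacam: 0.20 × 40 = 8 patients with change.
- LiveOCT: 0.50 × 40 = 20 patients.
- The plan expects LiveOCT to detect every Pentacam change, so the standard-only cell is assumed to be 0.
- LiveOCT only: 20 − 8 = 12 of 40.

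All 12 come from the 40 − 8 = 32 patients whom the Pentacam calls unchanged: 12 / 32 = 37.5%. The study needs to know how much of this could be false change.

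**4. What the healthy group could tell.** If 0 of 20 healthy volunteers were flagged, the one-sided 95% upper bound is 1 − 0.05^(1/20) = 13.9%. With 18 analysed (10% dropout) it is 1 − 0.05^(1/18) = 15.3%. If 13.9% also applied to the 32 Pentacam-negative keratoconus patients (an assumption), false change would account for at most about 0.139 × 32 = 4.5 of the expected 12. So even a group of 20 is informative against the effect the plan hopes for.

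**5. False calls with no true change (illustration; the rates are assumed, not in the protocol).** Let each method falsely flag one feature independently with rate f. The LiveOCT-only share is f(1 − f).
- f = 5%: 0.05 × 0.95 = 4.75%, or 3.3 of the 70 patients.
- f = 10%: 0.10 × 0.90 = 9%, or 6.3 of 70.
- If instead 10% is a per-scan rate, scans are independent, and two of three must agree (also assumed): 3 × 0.1² × 0.9 + 0.1³ = 2.8%, or about 2 of 70.

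An equal number would be expected in the uncounted standard-only cell if both methods had the same final rate.

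**The case against.** The strongest reply is that the paragraph must be read whole. It asks whether changes track disease status, whether features are reproducible and whether the information is redundant, so it can return a null answer. This stands. A reader might infer that the outcome can only favour LiveOCT; the text does not support that. It cannot find LiveOCT worse, which is a narrower statement.

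Replication is the second reply: three captures per device per visit filter out independent scan noise, as the last line of the illustration shows. This also stands for noise within a sitting. But Study design has all measurements on a device taken together to avoid delays from positioning the patient. Agreement within one sitting does not exclude repositioning or drift between visits, and change between visits is what this outcome reads.

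Third, LiveOCT misses are partly covered elsewhere. Secondary sensitivity asks whether LiveOCT detects the diagnostic features seen on the Pentacam and slit lamp, and Bland-Altman agreement is planned. That is a partial answer: sensitivity is secondary, is framed around diagnostic features rather than change between visits, and its specificity definition names no disease-free group.

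Fourth, a reader might infer that the study has no negative control. It has one: 20 healthy volunteers on the same schedule, with a stated expectation of little TCT change. Only this outcome fails to use them.

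Finally, a reader might infer that images are read with diagnosis and visit order known. The protocol does not say so. Masking commonly belongs in the SAP or a reading manual and is no finding here.

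**Conclusion.** The point holds in limited form. As defined, the added-information outcome counts one direction of disagreement, in the diseased groups only. It can return a null or redundant result, but it cannot show LiveOCT to be worse and cannot separate true added information from false LiveOCT change between visits. On the plan's own figures this affects the cell expected to hold about 12 of 40 keratoconus patients. That number rests on the plan's 20%, its 50% and its expectation that LiveOCT misses nothing the Pentacam shows. No corresponding rates are given for the FECD group.

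The conclusion does not depend on the assumed false-call rates, which only illustrate the mechanism. They should not be read as estimates, and larger figures obtained by multiplying features together would have no basis in the document.

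This is worth correcting in the protocol, because it concerns the definition of a primary outcome and the data needed will already exist.

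**What to change.** Amend the added-information paragraph under Primary outcomes in two ways.

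1. For each feature that both LiveOCT and a standard instrument can measure, cross-classify change as both, LiveOCT only, standard only or neither. Report both discordant proportions with 95% confidence intervals.
2. For all features, report the LiveOCT change rate in the 20 healthy volunteers beside the rate in each disease group, using the same criteria. This includes features that only LiveOCT can measure, such as Bowman's layer, for which the protocol says there is no Pentacam comparison.

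The split matters. Where the standard instrument cannot measure a feature, the standard-only cell is empty by construction, so a paired test of the two discordant cells would itself favour LiveOCT. There the healthy rate is the usable reference.

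Cost: some extra reading and analysis of images already collected, with no added participants, visits or scans. Limits: precision at n = 20 is modest (upper bound about 14% even with none flagged). The healthy rate may also understate false change in diseased corneas; the sample-size text itself uses different Pentacam cut-offs, 12.1 µm for change in keratoconus and 8.81 µm for healthy subjects. It is a reference rate, not a correction factor.
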